### Analysis

Monthly reports will be generated to monitor referral patterns to the Thrive clinical pathway. The primary analysis will use a mixed-effects negative binomial regression model, accounting for both medical team and time effects, to evaluate readmission and ED utilization patterns comparing those with and without SMI who receive Thrive to those with and without SMI who receive usual care [26,27]. Sensitivity analyses may include logistic regression, depending on data distribution.

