### Power Analysis

Based on a power analysis, a sample size of 472 (236 Thrive participants and 236 usual care) for the outcome of readmissions, or a sample of 534 (267 Thrive participants and 267 usual care) for the outcome of ED visits, will yield 80% power to detect significance at the *P*<.05 level. Our goal is a sample size of 534 to ensure adequate power for both outcomes. This assumes a 20% (106/534) loss to follow-up rate. Furthermore, assuming at least a third of the patients will have SMI and an overall 30-day readmission rate of 28% (44/160), a sample of 534 patients will have 80% power to detect an odds ratio as small as 1.46, comparing those with and without SMI, to be statistically significant at the *P*<.05 level. Power analyses were conducted using Power Analysis and Sample Size 2021 (NCSS Statistical Software) [28].

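### The stated 80% power for an SMI odds ratio of 1.46 does not follow from its inputs: 534 patients give about 47% power at 1.46 and reach 80% only at about 1.75

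*Protocol article*

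**What the plan says.** The Power Analysis section (Aim 2) first gives totals for Thrive versus usual care: 472 for readmissions and 534 for ED visits. It adopts 534 as the goal and adds that this assumes 20% loss to follow-up (106 of 534). It then turns to the SMI comparison, "assuming at least a third of the patients will have SMI" and an overall 30-day readmission rate of 28% (44 of 160). From these it concludes that "a sample of 534 patients will have 80% power to detect an odds ratio as small as 1.46", with the contrast being between those with and without SMI, "to be statistically significant at the *P*<.05 level". The section names the software package, but not the procedure used or whether the test is one- or two-sided.

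**The concern.** The odds ratio of 1.46 is the only effect size in the power section; the 472 and 534 totals are given without one. It is therefore the only statement of how small a difference the trial could detect. It bears on a stated hypothesis: Aims and Hypotheses expects worse utilization outcomes with SMI than without under usual care.

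The figure looks too small for the sample. At a 28% event rate, an odds ratio of 1.46 is a difference of under 8 percentage points, tested with 178 patients in the smaller group. If the claim is wrong, a reader who trusts it could take a non-significant SMI difference as ruling out an odds ratio of 1.46, when the trial would miss a true difference of that size slightly more often than it would find it.

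**Working it through.** **Inputs, all from the Power Analysis section:** N = 534; SMI share f = 1/3, so n1 = 178 and n0 = 356; overall rate 0.28; odds ratio 1.46; alpha 0.05. Two-sided testing is my assumption, varied below.

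**Step 1, group rates.** Solve (2/3)p0 + (1/3)p1 = 0.28 with [p1/(1−p1)]/[p0/(1−p0)] = 1.46. This gives p0 = 0.2540 and p1 = 0.3320, a difference of 0.0780.

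**Step 2, power at 1.46.** Power = Φ[(p1 − p0 − 1.96·s0)/s1], where
- s0 = √[0.28 × 0.72 × (1/178 + 1/356)] = 0.0412
- s1 = √[p1(1−p1)/178 + p0(1−p0)/356] = 0.0422

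Power = Φ[(0.0780 − 0.0808)/0.0422] = Φ(−0.065) = **47.4%**, against the stated 80%.

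**Step 3, check on the log-odds scale.** ln 1.46 = 0.378 and its standard error is 0.200, so z = 1.89 and power = Φ(1.89 − 1.96) ≈ 47%. A simulation of 200,000 trials gave 47.2%.

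**Step 4, detectable odds ratio.** Raising the odds ratio until Step 2 returns 80% gives **1.752**, with p0 = 0.241, p1 = 0.358 and risk ratio 1.48.

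**Step 5, patients needed.** 80% power at 1.46 takes about 1,185 to 1,188 analysed patients, depending on rounding. That is more than twice 534.

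**Step 6, attempts to recover 80% at 1.46**

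| Reading | Power at OR 1.46 | OR at 80% power |
|---|---|---|
| Base case (1/3 SMI, two-sided, N = 534) | 47% | 1.75 |
| 27.5% (44/160 exactly) instead of 28% | 47% | 1.76 |
| Half with SMI | 50% | 1.72 |
| One-sided | 60% | 1.65 |
| One-sided and half with SMI | 62% | 1.62 |
| 668 analysed, two-sided | 56% | 1.65 |
| 668 analysed, one-sided, half with SMI | 71% | 1.54 |

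Taking 28% as the no-SMI rate instead of the overall rate gives 49% two-sided, and 65% one-sided with half having SMI. No odds-ratio reading tried with SMI as a two-group factor reaches 80%.

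**Step 7, the stated loss.** 534 − 106 = 428. With a third having SMI and a two-sided test, power at 1.46 is **39.8%** and the detectable odds ratio is **1.87**.

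**Step 8, 1.46 read as a risk ratio.** With 28% overall, p0 = 0.28/(2/3 + 1.46/3) = 0.243 and p1 = 0.354. Power is 77% with 534 analysed and 67% with 428. With 28% as the no-SMI rate and 534 analysed it is 85%.

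**The case against.** **The section does not give every setting.** Sidedness and the software procedure are unstated, so the sponsor's exact calculation cannot be replayed. That is true, but the one-sided variants stay well below 80%. A procedure for a continuous standardised covariate does not give 1.46 either: its detectable odds ratio is 1.31, and SMI is a yes/no factor here.

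**The number may be right and the label wrong.** Read as a risk ratio, 1.46 has 77% to 85% power with 534 analysed, close to the claim. This stands as a serious possibility and shapes the fix. It is not an exact match and nothing in the text confirms it, so it remains an inference. If true, the sentence still needs correcting.

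**1.75 is itself optimistic.** The same section assumes 20% loss, so a replacement based on 534 alone could again overstate sensitivity. This stands, and both analysed numbers should be shown.

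**The consequence is limited.** The 534 goal comes from the ED-visit comparison of Thrive with usual care. The SMI sentence is an addition to it, and correcting that sentence changes neither enrolment nor design. This stands too.

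**Stronger readings a reader might infer.** One is that the trial's sample size is wrong. The documents do not support that: the effect sizes behind 472 and 534 are not given, so those totals cannot be tested this way. Another is that the shortfall can be quantified on the primary model's scale, since "The primary analysis will use a mixed-effects negative binomial regression model". The article gives no dispersion or mean event count, and an odds ratio of 1.46 at these rates is a risk ratio of only about 1.31 (0.332/0.254), so it cannot be carried over as a rate ratio of 1.46.

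**Conclusion.** The claim is wrong as written. On the section's own inputs, power at an odds ratio of 1.46 is about 47%, roughly 33 percentage points below the stated 80%, and the odds ratio detectable with 80% power is about 1.75. If the stated loss leaves 428 analysed, the figures are about 40% and 1.87.

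These results assume an unadjusted, two-sided comparison of two proportions at 0.05, exactly one third with SMI, and 28% as the overall rate. Other choices of sidedness, SMI share and base rate leave power at 1.46 no higher than about 65% with 534 analysed. Clustering is not allowed for and would generally lower power further. The finding concerns only the SMI comparison and says nothing against the Thrive versus usual care totals. How 1.46 arose is not established.

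**What to change.** First check the power output to see whether 1.46 was produced as an odds ratio or a risk ratio, and with which sidedness and analysed number. Then restate the sentence in one of these forms:

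- **80% power kept:** detectable odds ratio about 1.75 with 534 analysed (24.1% v 35.8%), and about 1.87 with 428 after the stated loss.
- **Odds ratio 1.46 kept:** power about 47% with 534 analysed, and about 40% with 428.
- **If 1.46 was a risk ratio:** relabel it and give its power, about 77% with 534 analysed and about 67% with 428, at 28% overall.

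Add that a non-significant difference between patients with and without SMI does not exclude an odds ratio below the detectable size. Because analysis is planned for early 2026, the correction should be on record before the SMI result is interpreted.

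The cost is a corrected sentence, one added caution and a less favourable stated sensitivity. No extra patients or data are needed.

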### Aim-3 Methods

Aim 3 is to evaluate the acceptability, appropriateness, feasibility, and cost-benefit of an adapted Thrive clinical pathway that is tailored for Medicaid-insured patients with co-occurring SMI.

#### Design

Guided by Woodwards’ HEIF and using a mixed methods approach, we will survey and interview patients, organizational leaders, and health care providers to determine if HEIF domains including cultural factors, clinical encounters, and societal context are associated with uneven or disparate benefits to the intervention.

#### Sample

##### Patients

Using a convenience sampling approach, the project manager (PM) will invite patients referred to Thrive to provide feedback on their experiences with the interventions. If Thrive participants agree, the PM will enroll and obtain consent shortly after discharge. Refusal to participate in an interview does not exclude the patient from getting Thrive services. We will attempt to recruit up to 40 patients for interviews (20 with SMI and 20 without). For participants with a history of psychosis, we will complete the Evaluation of the Capacity to Sign Consent to assess their ability to participate in the interviews or survey. Thrive participants will be excluded from interviews if they are (1) incapable of participating in a group discussion or understanding content as determined by the Evaluation of the Capacity to Sign Consent or (2) experiencing an acute cognitive impairment or intellectual disability.

##### Clinicians

Fifteen clinicians (eg, physicians, advanced practice providers, nurse case managers, and home care nurses) will be recruited to participate in interviews at the end of the study. These professionals will provide critical insights into the feasibility, appropriateness, and workload involved in referring patients to the expanded Thrive clinical pathway.

##### Health Care Leaders

We will recruit 5 leaders at HUP-Cedar and Penn Medicine at Home to assess the broader contextual factors affecting the acceptability and implementation of Thrive. These will take place at the end of the study.

#### Data Collection

##### Qualitative Data Collection

Interview guides will be developed using our previous experience piloting Thrive, the domains of the HEIF, and Proctor’s implementation outcomes. Questions will be tailored for patients and clinicians and may include perceptions of bias, culturally relevant care, discrimination, acceptability of Thrive, and feasibility of its delivery. During interviews, participants will be asked for permission to audio record the interview. If the participant consents to the interview but does not agree to recording, the interviewer will take detailed notes during the conversation. Demographics of clinicians and administrators will also be collected. Directly following the interview, the interviewer will record field notes to add details not apparent from a transcript. Audio recordings will be labeled with a unique ID number. They will be uploaded to a secure server and transcribed by ADA Transcription, a transcription company with considerable experience in qualitative research, HIPAA (Health Insurance Portability and Accountability Act) regulations, and confidentiality. Cleaned transcripts will be entered into NVivo 14 (Lumivero) for coding and analysis. All interview participants will receive a US $50.00 gift card for participation.

##### Quantitative Data Collection

At the beginning of their interviews, clinicians and patients will be asked to complete a 12-item survey based on Proctor’s implementation outcomes, assessing acceptability (how fair or reasonable Thrive is deemed), appropriateness (to what extent Thrive seems suitable), and feasibility (the practicality and ease of delivering Thrive). Each construct has a 4-item instrument with a 5-point Likert scale that asks participants to rate the degree of agreement or disagreement with each item. Each instrument is averaged with higher scores indicating greater acceptability, appropriateness, or feasibility [29].

##### Cost-Benefit Data

The cost of Thrive will be calculated from budget monitoring data for the research budget and the cost of staff time [30]. Postdischarge use (ie, readmissions and ED use) will be derived from the EHR. Average Medicaid facility fee payments per admission will be obtained from the Pennsylvania Health Care Cost Containment Council, an independent state agency responsible for addressing health costs [31].

#### Analysis

In our concurrent mixed methods approach, surveys and interviews will be collected at the same time. Summary statistics will be produced from the quantitative measures of acceptability, appropriateness, and feasibility. All interview data will be stored and analyzed on NVivo version 14 using constant comparative analysis to examine data across cases.

#### Triangulation of Quantitative and Qualitative Data

Using a convergent, parallel, mixed methods design [32-34], analyses will be conducted simultaneously for the surveys and interviews. This design will allow us not only to compare the quantitative and qualitative findings but also to validate and expand our quantitative results using qualitative data. Integration of the results will occur during analysis and interpretation to confirm or cross-validate findings. Using the HEIF as an organizing framework, we will look for linkages between our findings from the quantitative analysis and related themes that emerge from the qualitative data [35].

#### Cost-Benefit Analysis

The cost of Thrive will be calculated from budget monitoring data for the research budget and the cost of staff time [30]. We will use the number and acuity of inpatient admissions to estimate the costs paid by Medicaid for patients who received Thrive compared with usual care. In Pennsylvania, Medicaid pays by hospital admission; so, to estimate inpatient costs, we will use the average Medicaid facility fee payment per admission reported by the Pennsylvania Health Care Cost Containment Council and increase it by 17.7% to reflect typical Medicaid professional fees as a percentage of facility fees [36,37]. We will adjust this inpatient admission cost estimate to reflect the acuity of admissions as follows. First, we will estimate the acuity of each admission by multiplying its diagnostic-related group code by standardized case-mix weights published by the Centers for Medicare and Medicaid Services [31]. We will average these case-mix weights by study arm and divide them by the average case-mix weight for all Medicaid discharges in our dataset. We will multiply these arm-specific adjustment factors by the Medicaid cost per admission to arrive at an acuity-adjusted average cost of admission for each arm.

### Ethical Considerations

The study has received approval from the University of Pennsylvania institutional review board (#8, Protocol 854422 on October 4, 2023), including a HIPAA waiver of informed consent for clinical data derived from the EHR. All study data collected will be deidentified, and participants will be assigned a pseudoidentifier. No individual participant will be identifiable in any published materials. Data will only be accessible on password-protected computers available to the study team. Written consent will be obtained before patient, clinician, and health system leader interviews. Interview participants will be compensated US $50.00 by gift card. The study will be conducted according to national regulations and the Declaration of Helsinki**.**

### Dissemination

Our team will lead extensive efforts to disseminate our findings, emphasizing the expanded scope of Thrive to thoroughly address the mental health needs of patients with co-occurring SMI. We will use various channels, including publications; conference presentations; policy briefs; and engagement with both national and international networks through the Penn School of Nursing Communication Office, Leonard Davis Institute of Health Economics, and the Center for Health Outcomes and Policy Research. Planned dissemination activities include (1) up to 5 publications (at least 1-2 per aim); (2) annual scientific presentations and conferences; (3) infographics and guest appearances on relevant podcasts (eg, Amplify Nursing); and (4) development of a comprehensive Thrive website, featuring open-access modules on the components and implementation processes of the expanded program. We will also engage with our Thrive Community Advisory Board quarterly to ensure our dissemination efforts are equity-focused and resonate with health system and community stakeholders.

## Results

Our research was funded in October 2023. Data collection began in April 2024 and is expected to continue through December 2025. As of October 17, 2024, a total of 46 patients have been referred to Thrive. We will conduct data analysis early in 2026. We anticipate publishing results in 2025-2027.

## Discussion

### Expected Findings

We anticipate that patients with and without co-occurring SMI will benefit from Thrive enrollment and experience less unfavorable use (ie, readmissions and ED visits) and more favorable use (ie, primary care, specialty, and connections to community-based resources) than those receiving usual care. We also anticipate the adapted version of Thrive to be deemed feasible, acceptable, and appropriate by patients, clinicians, and health system leaders.

### Comparisons with Previous Work

Transitional care programs that focus on patients with SMI most often do not include a comprehensive plan to address integrated medical and psychiatric conditions [9-11]. In addition, there is a lack of focus on addressing SDOH, which are driver of both physical and mental health outcomes. For example, programs like the mobile health transitions of care program for adults with schizophrenia spectrum disorders aim to support patients with SMI in the critical period following hospital discharge through mobile health technologies [38]. Similarly, models such as the Depression and Coleman Care Transitions Intervention focus specifically on mental health conditions like depression, without integrating care for co-occurring physical health issues [9].

### Strengths and Limitations

The major strength of our study is the use of a stepped-wedge, cluster randomized controlled trial design. This allows all eligible patients at our study hospital the opportunity to be referred to Thrive during the study window. One limitation is the use of EHR data for our usual care group, as we can only capture use that occurs within our health system.

### Conclusion

This study is poised to advance the field of equity-focused, evidence-based interventions by testing the effectiveness of Thrive in improving care transitions for patients with Medicaid insurance and co-occurring SMI and examining Thrive’s implementation at a new site. The infusion of equity-focused principles in the design and evaluation of Thrive is anticipated to contribute substantially to both implementation and effectiveness outcomes, offering critical insights into how these principles can enhance health care delivery for patients with the highest health-related social needs.

## Appendix

Multimedia Appendix 1 Reporting checklist for protocol of a clinical trial based on the SPIRIT (Standard Protocol Items: Recommendations for Interventional Trials) guidelines.

Multimedia Appendix 2 CONSORT (Consolidated Standards of Reporting Trials) checklist for stepped wedge trials.

Multimedia Appendix 3 Summary of outcomes, measures, data sources, collection method, and time.

Multimedia Appendix 4 Peer Review Feedback from the Agency for Healthcare Research and Quality.

## Abbreviations

CONSORT: Consolidated Standards of Reporting Trials
ED: emergency department
EHR: electronic health record
HEIF: Health Equity Implementation Framework
HIPAA: Health Insurance Portability and Accountability Act
HUP: Hospital of the University of Pennsylvania
ICD-10: International Classification of Diseases, Tenth Revision
PM: project manager
SDOH: social determinants of health
SMI: serious mental illness
SPIRIT: Standard Protocol Items: Recommendations for Interventional Trials
